| Objectives, Specific Aims and Rationale Overall aim  To investigate ethnic differences in prescribing for type 2 diabetes in UK primary care.  Objectives  For people of European, South Asian and African Caribbean origin, ethnic differences in the following will be investigated:   1. Proportions of people with: a) incident hypertension started on antihypertensives and b) an elevated 10 year CVD risk score (according to QRISK, ASSIGN, JBS2, Framingham or unspecified risk-estimating equations (26)) being commenced on statin treatment. 2. Time to initiation of first-line anti-diabetic/ antihypertensive/lipid-lowering medication 3. Choice of anti-diabetic (first- to third-line), antihypertensive and lipid-lowering medication 4. Doses used for each anti-diabetic, antihypertensive and lipid-lowering medication 5. Monitoring rate after medication commencement 6. Time to medication intensification (up-titration, addition or switching) after detection of sub-optimal control of diabetes, hypertension or blood lipids   Additionally, we will examine potential confounding or mediating role/s of:   1. Smoking, BMI, deprivation, polypharmacy, multi-morbidity, drug adherence (for objectives v) and vi)), patient engagement with healthcare, diabetes duration and HbA1c (in people with diabetes).   Null hypotheses   1. No ethnic difference in proportions of people started on a) antihypertensives or b) statin treatment will be detected. 2. No ethnic difference in time to initiation of first-line anti-diabetic, antihypertensive or lipid-lowering medication will be detected. 3. Regarding choice of medication: 4. No ethnic difference in the proportions of people prescribed metformin as first-line, or sulphonylureas, DPP4-inhibitors, thiazolidinediones, SGLT2 inhibitors, GLP1 agonists or insulin as second- or third-line diabetes treatment will be observed. 5. No ethnic difference in the proportions of people prescribed ACE inhibitors/ angiotensin-receptor blockers, calcium-channel blockers or thiazide diuretics for hypertension will be observed. 6. No ethnic difference in the proportions of people with ≥10% cardiovascular disease risk who are prescribed lipid-lowering medication will be observed. 7. No ethnic difference in the proportions prescribed the maximum dose of anti-diabetic, antihypertensive or lipid-lowering medication will be observed, and the modal dose for each class will not differ by ethnicity. 8. No ethnic difference in the monitoring rates of anti-diabetic, antihypertensive or lipid-lowering medication will be observed. 9. No ethnic difference in time to treatment intensification (after the detection of sub-optimal control) of anti-diabetic, antihypertensive or lipid-lowering medication will be observed. 10. Associations between ethnicity and prescribing will not be confounded or mediated by smoking, BMI, deprivation, polypharmacy, multi-morbidity, drug adherence, patient engagement, diabetes duration or HbA1c (in people with diabetes).   Rationale  Research indicates that control of diabetes and its allied cardiovascular risk factors is poorer in UK’s minority ethnic groups than in the background white population. Crucially, these discrepancies are likely to contribute to higher rates of heart disease and stroke, in people with and without diabetes, seen in these groups. By examining the associations above, this study seeks to determine whether ethnic differences in prescribing for people with and without diabetes are present, and explanations for them.  It is important to compare prescribing in people with and without diabetes for each ethnic group. Our previous work suggests that diabetes is a much more potent CVD risk factor in people of South Asian and African Caribbean-origin than those of European-origin, and differential prescribing of statins and anti-hypertensives in those with vs. without diabetes is a possible explanation for this.  If ethnic inequalities in prescribing are present, their identification may influence future prescribing recommendations and thus eventually lessen the personal and societal burden of diabetes and cardiovascular disease complications in ethnic minority groups. |

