| L. Definition of the Study population All permanently-registered patients with research-standard data and incident type 2 diabetes Read codes from at least 1 year after 1^st^ January 2006 (start of follow-up; coinciding with when ethnicity was recorded for ≈80% of new registrations (17)) to 31^st^ December 2018 in the CPRD. The study will be restricted to incident cases to enable more precise measurement of treatment stage; people with prevalent type 2 diabetes Read codes prior to 2006 will be excluded.  Type 2 diabetes will be defined by a previously tested algorithm that uses Read codes, medication, blood test results and diabetes-specific process of care Read codes to adjudicate diabetes status (27) – see appendix. Specific exclusions will include: type 1 diabetes, gestational diabetes, non-specified diabetes diagnosed at ≤40 years in Europeans or ≤35 years in South Asians and African Caribbeans (reducing misclassified type 1 diabetes), and secondary diabetes (e.g. drug-induced).  In people without diabetes, those eligible for antihypertensive treatment will include people ≥40 years of age with incident: Read codes for hypertension, clinic BP of ≥160/100, ambulatory BP of ≥150/95 or clinic BP of ≥140/90 or ambulatory BP of ≥135/85 **plus either** 10 year CVD risk score exceeding 20% or 10% (for calendar years 2006-2013 and 2014-2019 respectively) **or** evidence of target organ disease (i.e. Read codes for left ventricular hypertrophy, chronic kidney disease, micro/ macroalbuminuria, or hypertensive retinopathy) (24). Those eligible for lipid-lowering medication will include people ≥40 years of age with an incident recording of CVD risk score ≥20% (if recorded between 2006 and 2013), or ≥10% (if recorded between 2014 and 2019), to account for guidelines changes (26)) during the study period. |

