| O. Data/ Statistical Analysis For all parts of the study, the population will be people with and without new-onset type 2 diabetes active in CPRD from 2006 (see section K, above) and the exposure will be ethnicity (either South Asian vs. European [baseline] or African Caribbean vs. European [baseline], as detailed in section L, above). Covariates in base models will include age and sex, and further covariates will be considered individually, as outlined in section vi) below. Statistical analysis is further considered by objective:   1. **Outcome:** Proportion of those eligible for primary prevention who are prescribed a) antihypertensives and b) lipid-lowering medication   **Entry:** Date of incident a) hypertension Read code/ raised BP reading or b) elevated 10 year CVD risk score, at least 12 months after study start date of 1^st^ January 2005  **Exit:** First of; date of first antihypertensive/ lipid-lowering medication prescription (defined by the absence of a prescription for the medication in the previous 6 months’ records), end of study, leaving CPRD practice or death  **Analysis:** Proportions receiving antihypertensives/ statin will be compared by ethnicity, then logistic regression models will be used to adjust for confounding/ investigate potential mediators  **Example effect measure:** Odds ratio (OR) of receiving an antihypertensive/ lipid-lowering medication vs. not for each ethnic group of interest, stratified by time period since identification of hypertension/ elevated CVD risk   1. **Outcome**: time to initiation of first-line anti-diabetic/ antihypertensive/ statin, probability of receiving anti-diabetic/ antihypertensive/ statin at one year post-diagnosis/ identification of high CVD risk   **Entry**: date of type 2 diabetes diagnosis/ incident hypertension Read code or raised BP reading/ incident high 10 year CVD risk score recording  **Exit**: date of first anti-diabetic/ antihypertensive/ statin prescription (defined by the absence of a prescription for the medication in the previous 6 months’ records), or end of study/ leaving CPRD practice/ death  **Analysis**: summary statistics will be compared by ethnicity using Kaplan-Meier time-to-event analysis (cumulative failure probability in a given time frame by ethnicity, comparison of medians by log-rank test), Cox proportional hazards regression models will be used to adjust for confounding/ investigate potential mediators  **Example effect measure**: hazards ratio (HR) for anti-diabetic/ antihypertensive/ statin prescription   1. **Outcome:** proportions of patients prescribed medication from each anti-diabetic (stratified by first- to third-line treatment), antihypertensive and lipid-lowering class (defined by the absence of a prescription for the medication in the previous 6 months’ records)   **Sub-population:** a) all participants starting first- to third-line anti-diabetic treatment, b) all patients on antihypertensives, or c) all patients on lipid-lowering medication  **Analysis:** proportions receiving each drug will be compared by ethnicity, then logistic regression models will be used to adjust for confounding/ investigate potential mediators  **Example effect measures**: odds ratio (OR) of being prescribed metformin (=1) vs. non-metformin medication (=0) at first stage of treatment, OR of being prescribed sulphonylurea (=1) vs. non- sulphonylurea medication (=0) at second stage of treatment, OR of calcium-channel blocking antihypertensive prescription vs. non- calcium-channel blocking antihypertensive in those on antihypertensive treatment, OR of statin prescription vs. non-statin lipid-lowering medication prescription in those with >10% 10 year cardiovascular risk   1. **Outcome:** proportions of patients prescribed each dose of each anti-diabetic, antihypertensive and lipid-lowering medication, stratified by treatment stage (defined by the absence of a prescription for the medication in the previous 6 months’ records)   **Sub-population:** a) all participants on first- to third-line anti-diabetic treatment, b) all patients on antihypertensives, or c) all patients on lipid-lowering medication  **Analysis: :** proportions receiving each dose of each drug will be compared by ethnicity, then logistic regression models will be used to adjust for confounding/ investigate potential mediators  **Example effect measures**: OR of being prescribed maximum dose (2g daily) vs. sub-maximum dose of metformin, OR of being prescribed atorvastatin 10mg per day vs. higher doses (20mg, 40mg or 80mg)   1. **Outcome:** yearly monitoring rate post commencement of medication from each anti-diabetic (first- to third-line), antihypertensive and lipid-lowering class – i.e. number of times HbA1c/ blood pressure/ blood lipids measured per person-year of follow-up, stratified by year after commencement; may be multiple entry dates per person for different medications   **Entry:** first use of any medications of interest from 2006 onwards  **Exit:** first of; end of strata (e.g. 1 year after medication commencement), end of study/ leaving CPRD practice/ death  **Analysis:** summary statistics will be compared by ethnicity, Poisson regression modelling used to adjust for confounding/ investigate potential mediators  **Example effect measures**: yearly monitoring rate ratios (RRs)   1. **Outcome:** time to medication intensification (up-titration, addition or switching) after detection of sub-optimal control of diabetes, hypertension or blood lipids, or probability of intensification 1 year post-detection of sub-optimal control; may be multiple entry dates per person for different medications   **Entry:** date when sub-optimal risk factor control detected (see section M for how this is defined for each risk factor)  **Exit:** first of; date of anti-diabetic, antihypertensive or lipid-lowering treatment intensification, end of study/ leaving CPRD practice/ death  **Analysis:** summary statistics will be compared by ethnicity using Kaplan-Meier time-to-event analysis (cumulative failure probability in a given time frame by ethnicity, comparison by log-rank test), Cox proportional hazards regression models will be used to adjust for confounding/ investigate potential mediators  **Example effect measures**: cumulative failure probability for each ethnic group 1 year post detection of sub-optimal value, comparison of median survival times using the log-rank test by ethnicity, HRs of intensification stratified by year   1. **Outcome:** influence of deprivation, polypharmacy, multi-morbidity, drug adherence (iv) and v) only), patient engagement with healthcare, diabetes duration and HbA1c on any ethnic differences found in i) to v).   **Entry:** as above for i), iv) and v)  **Exit:** as above for i), iv) and v)  **Analysis:** as above for i) to v)  **Covariates:** smoking status, BMI, deprivation, polypharmacy, multi-morbidity, drug adherence, patient engagement with healthcare, diabetes duration and HbA1c  **Effect measures:** we will observe the degree of attenuation of the ethnic difference effect measure for each outcome when each covariate is inserted in turn to models, and thus evaluate the likelihood of confounding or mediation  Sub-group/ sensitivity analyses  See section O of original application  Plans for addressing misclassification and bias  See section O of original application  Multiple comparisons  See section O of original application |

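### The amendment adds people without diabetes so that prescribing can be compared by diabetes status within ethnic groups, but no objective, null hypothesis or model makes that comparison

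*Supplement*

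**What the plan says.** All references are to the amendment of 9 December 2019 in the Supplement unless stated.

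- **Objectives, Specific Aims and Rationale.** The reason for the extension is given directly: "It is important to compare prescribing in people with and without diabetes for each ethnic group". The text adds that diabetes appears to be a stronger cardiovascular risk factor in the two minority groups, and that "differential prescribing of statins and anti-hypertensives in those with vs. without diabetes is a possible explanation for this". The listed objectives and null hypotheses all concern ethnic differences; none concerns how those differences vary with diabetes status.
- **Section O, Data/ Statistical Analysis.** A single definition serves every objective: "the population will be people with and without new-onset type 2 diabetes active in CPRD from 2006". The exposure is ethnicity. "Covariates in base models will include age and sex, and further covariates will be considered individually". The covariates to be added one at a time include diabetes duration and HbA1c, but not whether the person has diabetes.
- **Section N.** The comorbidities that define multimorbidity do not include diabetes.
- **Subgroups.** Section O refers back to the original application, which stratifies by age group and calendar time only.
- **Feasibility counts, Sample size considerations and section L.** These give people without diabetes their own eligibility rules and expected numbers.

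**The concern.** The rationale poses an effect-modification question: does the ethnic difference in statin or antihypertensive prescribing differ between people with and without diabetes? Answering it takes estimates in each group and a contrast between them. The analysis section provides neither.

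What follows depends on how section O is read. If both groups enter one model, each antihypertensive and lipid contrast averages over two populations. Where prescribing differs by diabetes status and the minority groups contain a larger share of people with diabetes, the pooled ethnic contrast moves even if prescribers treat every ethnic group alike. If separate cohorts are analysed, that problem goes away, but two sets of results with no planned contrast leave the reader to compare them by eye.

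There is also a sign that the covariates were not adapted to the wider population. Patient engagement in section N is still counted over the year before diabetes diagnosis, so it has no value for someone who never had one. Under the original application's complete-case rule, a model adjusted for it would drop the group that the amendment adds.

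**Working it through.** **1. Which people the new power rows describe.** The plan expects at least 94K European, 6K South Asian and 3K African Caribbean initiators of antihypertensives without diabetes, and takes 21% of eligible people to be untreated. Eligible = initiators / (1 − 0.21):
- 94/0.79 = 119.0K (plan: 119.4K)
- 6/0.79 = 7.6K (plan: 7.6K)
- 3/0.79 = 3.8K (plan: 3.8K)

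So the new antihypertensive row of Table 1 rests on people without diabetes alone. The new statin row (49K, 3K, 2K) comes from the high-risk counts, which are also given for people without diabetes. No row addresses the comparison by diabetes status.

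**2. Where diabetes status could have entered.** Objectives: no. Null hypotheses: no. Base model: age and sex only. Added covariates: duration and HbA1c, not status. Multimorbidity list: no. Subgroups: age group and time only. Interaction terms: none.

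**3. How far pooling could move a statin contrast.** Inputs from Feasibility counts and Sample size considerations: 64% on statins with type 2 diabetes; 24% in the high-risk group; Europeans 120.4K with and 49K without diabetes. Assume no ethnic difference within either group. Let each minority be a fixed fraction of the European count in both groups, with its diabetes count multiplied by k. The fraction cancels.

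Pooled odds(k) = (0.64 × 120.4k + 0.24 × 49) / (0.36 × 120.4k + 0.76 × 49)

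- k = 1 (also the European odds): 88.816/80.584 = 1.102, so OR 1.00
- k = 1.5: 127.344/102.256 = 1.245, OR 1.245/1.102 = 1.13
- k = 2: 165.872/123.928 = 1.338, OR 1.21
- k = 3: 242.928/167.272 = 1.452, OR 1.32

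The values of k are assumptions. The plan says only that ethnic minorities are over-represented among people with diabetes. For scale, Table 1 gives 1.15 and 1.18 as detectable for the statin outcome. They are labelled HRs, but a two-proportion calculation gives ORs of 1.15 and 1.19.

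**4. Whether the missing test is feasible.** Detectable ratio = exp[(1.960 + 1.282) × √(sum of the variances of the four log odds or log hazards)], with two-sided 5% and 90% power. Assumed diabetes denominators: 92.7K/8.1K/3.5K divided by 0.79 for antihypertensives, and 77.1K/6.7K/2.9K divided by 0.64 for statins.
- Antihypertensive initiation, ratio of HRs (variance 1/events, 79% initiating): South Asian exp(3.242 × 0.01765) = 1.06; African Caribbean exp(3.242 × 0.02530) = 1.09
- Statin prescribing, ratio of ORs (variance 1/[np(1−p)]): South Asian exp(3.242 × 0.04889) = 1.17; African Caribbean exp(3.242 × 0.06202) = 1.22

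On these assumptions the cohorts are large enough for the comparison.

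**The case against.** The strongest reply is that nothing in the plan says one model is fitted to both groups. Section L has a separate eligibility paragraph for people without diabetes, the counts are separate, the new Table 1 rows use that group alone, and the objectives confine diabetes duration and HbA1c to people with diabetes. This stands: pooling is the literal reading of section O, not a declared choice. It does not rescue the stated comparison, which neither reading includes.

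Other inferences that a reader might draw go too far:

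- **That the plan's own counts show bias.** Used as printed, they give a pooled South Asian OR of (7.44/6.06)/1.102 = 1.11. But that comes from unequal South Asian shares in rounded counts: 10.5/140 = 7.5% with diabetes and 3/56.5 = 5.3% without. One common share gives 1.00, and the African Caribbean figure is (3.424/3.176)/1.102 = 0.98. Both cohorts were apportioned by the same census, so they say nothing about diabetes being commoner in minorities.
- **That antihypertensive contrasts are distorted to a similar degree.** The plan's figures are 77% on treatment with diabetes and 79% treated among eligible people. These are different quantities, but they do not show diabetes driving that class.
- **That follow-up must end at diabetes onset.** The exits are prescription, "end of study, leaving CPRD practice or death". Onset after entry may lie on the pathway from ethnicity to prescribing, so keeping that follow-up is a defensible estimand.
- **That the calendar windows defeat the comparison.** Entry without diabetes is "at least 12 months after study start date of 1^st^ January 2005"; with diabetes it is "incident type 2 diabetes Read codes from at least 1 year after 1^st^ January 2006". The starts differ by at most a year, and stratification by time is planned. This is minor.

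The illustration also joins proportions and counts from groups that were not assembled as one eligible cohort. It shows a mechanism and does not forecast a result.

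**Conclusion.** The gap is real and should be closed before analysis. The amendment states a with-versus-without-diabetes question and plans no analysis of it. This conclusion needs no arithmetic and holds whether section O means one population or two.

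The confounding concern is conditional. It arises only if the groups are pooled, and a size can be illustrated for statins only: a null OR of 1.00 would become 1.13 to 1.32 for 1.5- to 3-fold over-representation, and would stay at 1.00 with none. The multipliers are assumed, and the calculation takes no ethnic difference within groups and equal ethnic shares before over-representation.

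The documents do not support saying that the authors chose a confounded pooled model, or that the question cannot be answered. The cohorts and data are there, and the detectable interaction ratios of about 1.06 to 1.09 (antihypertensives) and 1.17 to 1.22 (statins) suggest adequate precision. What is missing is the specification.

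**What to change.** In section O:

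1. Fit the antihypertensive and lipid-lowering models separately by diabetes status at entry, and say so.
2. Then fit a combined model with ethnicity, diabetes status and their product. Report the ratio of ORs or HRs with its 95% CI as the analysis of the stated rationale, restricted to a calendar period common to both groups.
3. Censor at incident diabetes in the group without diabetes as a sensitivity analysis only.

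In the objectives, add the matching objective and null hypothesis: that ethnic differences in antihypertensive and lipid-lowering prescribing do not differ by diabetes status. Where the combined model is adjusted for patient engagement, count consultations before cohort entry, so that the covariate exists for everyone.

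The cost is a few extra models and some added text. No new data are needed. The common calendar period gives up at most about a year of entries at the start, and the sensitivity analysis uses somewhat less follow-up.

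### In people without diabetes, lower-band blood pressure needs a second criterion to qualify, but the antihypertensive entry date (objectives 1 and 2) does not wait for it

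*Supplement*

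**What the plan says.** All references are to the amendment of 9 December 2019.

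**Section L (study population), people without diabetes aged 40 or over.** Some routes to antihypertensive eligibility stand alone: "Read codes for hypertension, clinic BP of ≥160/100, ambulatory BP of ≥150/95". The lower band, "clinic BP of ≥140/90 or ambulatory BP of ≥135/85", counts only in combination with one of two further items. The first is a "10 year CVD risk score exceeding 20% or 10% (for calendar years 2006-2013 and 2014-2019 respectively"). The second is "evidence of target organ disease (i.e. Read codes for left ventricular hypertrophy, chronic kidney disease, micro/ macroalbuminuria, or hypertensive retinopathy").

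**Section O, objective 1.** The outcome is the "Proportion of those eligible for primary prevention who are prescribed a) antihypertensives and b) lipid-lowering medication". Entry is the "Date of incident a) hypertension Read code/ raised BP reading or b) elevated 10 year CVD risk score". Odds ratios are to be stratified by time since hypertension or raised risk was identified.

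**Section O, objective 2.** Entry is the "date of type 2 diabetes diagnosis/ incident hypertension Read code or raised BP reading/ incident high 10 year CVD risk score recording". The analyses are Kaplan-Meier, log-rank and Cox, plus the probability of treatment at one year.

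For both objectives, follow-up ends at first prescription, end of study, leaving the practice or death.

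**The concern.** The entry rule for the antihypertensive arm names the blood pressure reading but not the second component that section L attaches to the lower band. It also does not say what happens to a prescription issued between the two dates.

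Take a patient with 145/92 in 2008, no hypertension code, and a first qualifying risk score in 2015. On the literal rule, follow-up starts in 2008, and seven years in which section L did not yet count this patient as eligible are recorded as time untreated. Membership also depends on the future. A similar patient who is treated soon after the reading and never scored or coded is not in the cohort, while one left untreated until a later score is.

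Time zero and cohort membership are therefore at stake for two objectives. If risk scoring or organ-damage testing happens sooner in one ethnic group than another, that difference would appear as a difference in prescribing delay even if prescribing after eligibility were identical.

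**Working it through.** **1. The two sections side by side**

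| Route (people without diabetes) | Eligible under section L | Entry under section O | Gap possible? |
|---|---|---|---|
| Hypertension Read code | at the code | at the code | no |
| Clinic ≥160/100 or ambulatory ≥150/95 | at the reading | at the reading | no |
| Lower band, second component already recorded | at the reading | at the reading | no |
| Lower band, second component recorded later | at the score or organ-disease code | at the reading | **yes** |

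I read the second-component condition as applying to the lower band only, since otherwise the higher thresholds would be redundant. Only the last row is affected. By contrast, the lipid arm is dated at the risk score itself, so its eligibility and entry coincide.

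I found nothing elsewhere that closes the gap. The bias section, carried over from the original application, does not address it. The engagement covariate counts consultations in the year before diabetes diagnosis, which has no meaning for the people affected.

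**2. The plan's own figure for this outcome**

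Table 1 gives a detectable HR of 1.02 for both ethnic comparisons. Inputs from the sample-size section are 119.4K Europeans, 7.6K South Asians, 3.8K African Caribbeans, α=0.05 (two-sided assumed) and power 0.90. The event proportion is taken as 1 − 0.21 = 0.79.

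Formula: ln HR = (1.960 + 1.282) / √(E·p(1−p)), with E = 0.79N.

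- South Asian: E = 0.79 × 127,000 = 100,330. With p(1−p) = 0.25, HR = 1.021. With the actual p = 7.6/127.0 = 0.060, HR = 1.044.
- African Caribbean: E = 0.79 × 123,200 = 97,328. With p(1−p) = 0.25, HR = 1.021. With the actual p = 3.8/123.2 = 0.031, HR = 1.062.

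The printed 1.02 therefore reproduces only with equal group sizes. A fair yardstick is 1.044 and 1.062, or 0.958 and 0.942 in the other direction.

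**3. Illustration of the bias**

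The documents give neither the share of patients on the affected route nor the gap between reading and second component. Everything in this step is assumed:

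- Gap G is exponential with mean 1.0 year in Europeans and 1.5 or 2.0 years in the comparison group. Patients are kept if G ≤ 5 years, whether or not they were treated first.
- The treatment hazard after eligibility is 0.7 per year in both groups, so the true HR is 1.00.
- The hazard before eligibility is 0, 0.35 or 0.7 per year.
- Follow-up is 5 years from the reading, with 200,000 simulated per group.

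Cox HR with time zero at the BP reading:

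| Comparison gap | Hazard before eligibility | 100% on route | 50% | 25% |
|---|---|---|---|---|
| 1.5 y | 0 | 0.81 | 0.90 | 0.95 |
| 1.5 y | 0.35 | 0.94 | 0.97 | 0.99 |
| 1.5 y | 0.7 | 1.00 | 1.00 | 1.00 |
| 2.0 y | 0 | 0.71 | 0.84 | 0.93 |
| 2.0 y | 0.35 | 0.90 | 0.96 | 0.98 |
| 2.0 y | 0.7 | 1.00 | 1.00 | 1.00 |

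Simulation error is about 0.01. With time zero at the last component, and anyone treated earlier left out, the HR was 0.99-1.01 throughout.

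**4. Absolute probabilities, even with equal gaps**

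The true 1-year probability from eligibility is 1 − exp(−0.7) = 0.503. With a mean gap of 1.0 year (rate 1) and no earlier treatment, the probability from the reading is 1 − (0.7e^(−1) − e^(−0.7))/(0.7 − 1) = 0.203. Dividing by P(G ≤ 5) = 0.993 gives 0.204 if everyone is on this route. At a 25% share it is (0.75 × 0.503 + 0.25 × 0.203)/(0.75 + 0.25 × 0.993) = 0.43. With equal gaps in both groups the HR stays at about 1.00.

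**5. A second set of assumptions**

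Here 79% are treated within 12 months of eligibility, nobody is treated earlier, and 10%, 30% or 50% have a later second component. Mean gaps of 6 months (Europeans) and 12 months (comparison) give HRs of about 0.92, 0.84 and 0.76. Gaps of 6 and 3 months give about 1.05, 1.11 and 1.19. The bias can run either way.

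**The case against.** **The entry wording may be shorthand.** Objective 1 concerns people who are eligible, and section O points back to the population section. The raised reading can therefore be understood as the date the section L definition is first met. This stands as a possible reading, so a reader should not infer that the plan definitely prescribes pre-eligible follow-up. But the text does not say it, and two programmers could code different index dates.

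**The threshold is not really undefined.** A reader might infer that nothing says whether the BP date or the score date selects 20% or 10%. Section L attaches the calendar years directly to the risk score, and the next sentence, on lipid-lowering eligibility, applies the same cut-offs by when the score was recorded. The score date is the natural reading, and a confirming phrase is enough.

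**The large hazard ratios need extreme inputs.** Values of 0.71-0.81 require everyone to be on this route and no prescribing before the second component. At half the treatment rate beforehand, a 1.5-year gap gives 0.94-0.99, and at an equal rate there is no bias. This stands in full.

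**The scope is narrow.** Only the antihypertensive arm of objectives 1 and 2 is touched, and within it only people without diabetes who lack a hypertension code or a higher-band reading and whose second component comes later. This also stands.

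**The remedy does not remove all selection.** Patients treated before they are scored remain outside the eligible cohort. This is correct, and it is why their number should be reported by ethnicity.

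**Conclusion.** Sections L and O do not match for one eligibility route, and the mismatch affects time zero and cohort membership. Taken literally, the entry rule counts time before eligibility as prescribing delay and selects patients on later records. That distorts time to initiation and the 1-year probability on this route. The ethnic contrast is biased only if the gap, or the share on the route, differs by ethnicity. The documents do not show that it does.

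No size can be derived from the plan. Under the stated assumptions with a 1.5-year comparison gap, the HR lies anywhere from 0.81 to 1.00, depending mainly on how much prescribing precedes the second component. It would be tempting to set these values against Table 1's 1.02 and call all of them detectable. That is unsound, because with the actual group sizes the limits are about 0.96 (South Asian) and 0.94 (African Caribbean). Some scenarios pass those limits and others do not. The reason to act is that the index date is open to two codings and is cheap to settle before analysis, not that a large bias has been shown.

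**What to change.** In section O, objectives 1 and 2, antihypertensive arm:

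1. For the lower-band route, define entry as the first date on which all required components are on record, that is, the later of the qualifying reading and the qualifying score or organ-disease code. Use only information recorded up to that date.
2. Confirm that the date of the risk score selects the 20% or 10% threshold.
3. Keep entry at the code or reading for the Read-code, ≥160/100 and ambulatory ≥150/95 routes.
4. State that patients already prescribed an antihypertensive before the entry date are not incident eligible initiators, and report their number by ethnicity.
5. Add a sensitivity analysis restricted to the stand-alone routes, which the mismatch cannot affect.

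The cost is a few lines of protocol text, a change to the index-date code and one extra analysis. Follow-up will be slightly shorter and entrants fewer on this route. Some selection remains from patients treated before they were scored, and items 4 and 5 make it visible without removing it.
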